### Statistical analyses

A multiple regression model (with e. g. ordinary least squares technique) is used to detect several predictors or mediators of cognitive decline. To identify the most parsimonious model, and with it the final predictors, we analyze the corresponding coefficients of determination and consider the multiple comparisons problem providing a proper method to counteract it. Additionally, we propose an alternative classification taking hand of the k-nearest neighbors algorithm. Furthermore, we analyze changes in motor, sensory, electroencephalogical, and cognitive parameters over time in all three groups using mixed-effects models to explain the correlations in repeated measures in the same subject. Hazard ratios of progressing to dementia for participants with cognitive, motor, sensory, and neurophysiological decline are obtained in the classical way using the Cox semi-parametric proportional hazard model. Several variables are included as potential confounders, such as sex, age, education, comorbidities, psychological status, and social support. The most appropriate procedure for handling missing data will be selected after inspecting the amount and pattern of missing data.

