#### Study design

The SENDA study is designed as a prospective cohort sequential study. After successful screening for study eligibility, participants are assigned to one of three study groups depending on their cognitive status based on their MoCA (Montreal Cognitive Assessment), CERAD-Plus (Consortium to Establish a Registry for Alzheimer’s Disease), and the FLei (‘Fragebogen zur geistigen Leistungsfähigkeit’, questionnaire for complaints of subjective cognitive disturbances) scores: 1. cognitively healthy individuals (CHI), 2. subjectively cognitively impaired persons (SCI), 3. possible mildly cognitively impaired persons due to inconclusive test results (pMCI), or mildly cognitively impaired persons (MCI). During the study period participants of four cohorts will be recruited at different time points (see Table 2). All participants complete the same cognitive, motor, sensory, and neurophysiological tests. Depending on the time point of study entry, all tests are repeated up to four times (time points: T1, T2, T3, T4) in intervals of 8 months within 3 years to identify associations with cognitive changes over time (see Fig. 1 for the study design and Table 2). The interval of 8 months was chosen according to Chamberlain et al. [55]. Only this frequency of follow-ups enables the measurements to be repeated up to three times in the defined funding period of 3 years. One test consists of three examination days of 1 to 2 h each.

**Table 2 Tab2:** Time points of study recruitment of the four cohorts and number of follow-up surveys (T1: Baseline; T2-T4: Follow-up surveys; ‘X’: participation; ‘-’: no participation)

Cohorts	T1	T2	T3	T4
Cohort 1 (begin: February 2018)	X	X	X	X
Cohort 2 (begin: July 2018)	X	X	X	-
Cohort 3 (begin: January 2019)	X	X	-	-
Cohort 4 (begin: January 2020)	X	-	-	-

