#### Cognitive status

All prior introduced neuropsychological assessments are used to establish the cognitive status of each participant at baseline and each follow-up. All criteria including cut-offs can be found in Table 3. Cognitive decline is defined as a change from CHI to SCI, pMCI, or MCI, as well as a change from SCI to pMCI or MCI or from pMCI and MCI to dementia. Individuals are categorized as having dementia when they receive a clinical dementia diagnosis outside of the study at any follow-up. Furthermore, participants are categorized as having dementia if they score less than 19 points in the MoCA [62] and perform worse than 1.5 SD below the norm in multiple cognitive domains of the CERAD-Plus. If so participants are advised to visit their general practitioner for further evaluation regarding dementia and to give a feedback to the study coordinator of SENDA as soon as possible. Additionally, functional limitations in ADL and the presence of depression will also be taken into account (see section ‘Questionnaire battery’).

**Table 3 Tab3:** Criteria for cognitive status of the participants

Group	Cognitive Status	Measures		
		MoCA	CERAD-Plus	Flei
Group 1	CHI	30–26	All tests within normal range (≤ 1.5 SD)	≤ 30
Group 2	SCI	30–26	All tests within normal range (≤ 1.5 SD)	> 30
Group 3	pMCI	30–26	1 or more tests below normal range (≥ 1.5 SD)	not considered
		< 26	All tests within normal range (≤ 1.5 SD)	not considered
	MCI	< 26	1 or more tests below normal range (≥ 1.5 SD)	not considered

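### The regression for cognitive decline, with least squares as its example and R-squared as its selection measure, does not fit a category-change outcome observed for 24, 16, 8 or 0 months

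*Protocol article*

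**What the plan says.** The Statistical analyses section gives the method for finding predictors of decline: "A multiple regression model (with e. g. ordinary least squares technique) is used to detect several predictors or mediators of cognitive decline". Selection follows: "To identify the most parsimonious model, and with it the final predictors, we analyze the corresponding coefficients of determination". The same sentence promises an unnamed method against multiple comparisons. A k-nearest-neighbour classifier is offered as an alternative. Mixed models are planned for change in the measured parameters, and a Cox model for progression to dementia. The named confounders are sex, age, education, comorbidities, psychological status and social support, in a list left open.

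The Cognitive status section fixes the outcome: "Cognitive decline is defined as a change from CHI to SCI, pMCI, or MCI, as well as a change from SCI to pMCI or MCI". The third route is from pMCI or MCI to dementia. No continuous decline score is defined.

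The Study design section says that "all tests are repeated up to four times (time points: T1, T2, T3, T4) in intervals of 8 months within 3 years". Table 2 shows four visits for Cohort 1, three for Cohort 2, two for Cohort 3 and one for Cohort 4.

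**The concern.** Three features of the outcome are not reflected in this regression.

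- **Scale.** Decline is a yes/no (or ordered) event. Least squares and R-squared are made for a continuous outcome.
- **Starting category.** By Table 3, a CHI participant at MoCA 26 or FLei 30 is recorded as declining after a change of one point. An MCI participant must receive a dementia diagnosis, or score below 19 on the MoCA and also fall below the norm in several CERAD-Plus domains. Better baseline cognition therefore puts a person where decline is easier to record.
- **Observation time.** Cohorts have three, two, one or no follow-up visits in which decline can be seen, and this model has no stated time element.

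In addition, the final predictors come from R-squared among many cognitive, gait, balance, fine-motor, sensory and EEG variables. The study's stated product is a detection instrument. An optimistic fit, or predictor effects blurred by starting category and follow-up, would go directly into it.

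**Working it through.** The article gives no expected decline rate, number of candidate predictors or model fit, so there is no figure of its own to reproduce here. Inputs from the article are the visit schedule, the definition of decline, the cut-offs and the MoCA retest reliability of .92. Everything else below is assumed.

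**1. Follow-up by cohort.** Months = (visits − 1) × 8:

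- Cohort 1: 3 × 8 = 24
- Cohort 2: 2 × 8 = 16
- Cohort 3: 1 × 8 = 8
- Cohort 4: 0, so no change can be observed.

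**2. Recorded decline at equal risk.** With risk q per interval and m intervals, the chance is 1 − (1 − q)^m. At q = .10:

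- m = 3: 1 − .9³ = .271
- m = 2: 1 − .9² = .190
- m = 1: .100

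That is a 2.7-fold difference between Cohorts 1 and 3 from the schedule alone. At q = .05 the figures are 14%, 10% and 5%; at q = .20 they are 49%, 36% and 20%.

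**3. Does this bias a predictor?** Simulation of a null predictor, 48 people per cohort, 5% test. If the predictor does not differ by cohort, the false-positive rate stays at 5%. If it differs by 0.2 to 0.5 SD per cohort step, the rate is 7% to 20%, and returns to about 5% once cohort is in the model.

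**4. Starting category.** Simulation with MoCA only: mean 25, SD 2.5, reliability .92, a predictor correlated .3 with cognition, and a mean drop of 0 to 1 point. Recorded decline is about 16% to 38% from MoCA 26 or above, against 0.3% to 2% from below 26. Odds ratios per SD of the predictor:

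- No effect on change: pooled 1.04 to 1.08; adjusted for baseline category 0.75 to 0.76.
- True protective effect of 0.3 MoCA points per SD: pooled 0.68 to 0.84; adjusted 0.49 to 0.53.

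With a real effect, the pooled estimate lies closer to 1. The first line also shows that adjusting for category alone is incomplete: it leaves an apparent association where there is none, because a noisy category captures only part of the true level. The gap between pooled and adjusted values is therefore not a clean measure of the attenuation.

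**5. Optimism of R-squared.** Choosing the best 5 of 60 noise variables by forward selection gives an in-sample R-squared of about .12 at n = 200 and .16 at n = 144. The 144 assumes equal cohorts after dropout: 240 × 0.8 = 192; 192 / 4 = 48; 3 × 48 = 144.

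A second simulation used a yes/no decline outcome, 144 people, three true predictors (log hazard ratio 0.4 per SD) and five variables chosen from 20, 40 or 80. Apparent R-squared was .13 to .23, against −.16 to .01 in new data.

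With 40 candidates, coefficients of true predictors that were selected averaged 0.065 against a population value of 0.042 (0.065 / 0.042 = 1.55), and 0.107 against 0.088 (1.21), at interval risks of 5% and 15%.

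**6. With a multiplicity method.** Bonferroni selection in the 40-candidate setting cut false selections to 0.03 to 0.05 per analysis. In the 34 and 91 of 300 runs where any predictor passed, apparent R-squared was .09 to .10, against −.03 to .01 in new data.

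**The case against.** The strongest reply is that the text commits to less than it seems to, and that other parts of the plan cover the ground.

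- **Least squares is only an example.** This is true, and the estimator could still be changed within the wording. The R-squared criterion carries no such qualifier.
- **The Cox and mixed models handle time.** They do, but for other targets: progression to dementia, and change in the measured parameters. Neither answers which variables predict a category decline. A reader might take the regression for the primary analysis. The article does not label it so, and its main research question concerns transition to dementia, which the Cox model addresses. Cognitive decline is, however, the outcome on which the sample size is based.
- **Multiplicity is addressed.** The sentence continues: "we analyze the corresponding coefficients of determination and consider the multiple comparisons problem providing a proper method to counteract it". That can control false selections well, as step 6 shows, but it does not remove the optimism in R-squared. The plan also seeks a parsimonious model, so a large retained set is not what it describes.
- **Coefficients need not be wrong.** A reader might infer that least squares must give wrong coefficients. It does not: without selection it recovered the population risk differences (0.041 against 0.042; 0.089 against 0.088). Unequal follow-up biases a coefficient only if predictors differ by cohort, which the article does not show.
- **Effects need not be reversed.** A reader might infer from pooled odds ratios just above 1 that true effects change sign. They arise with no effect on change, so they are close to the truth for change. With a real effect the result is attenuation.
- **The covariate list is open, and validation may be described elsewhere.** Both are fair. The absence of a validation plan from an article is not counted here; the point is the measure that the article does name.

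**Conclusion.** The point holds as a mismatch between the stated model and selection measure and the stated outcome. It does not hold as a claim that the coefficients will be wrong. The definition of decline and the unequal follow-up come directly from the article. Followed as written, the analysis mixes starting categories with very different chances of a recorded decline (about 16% to 38% against 0.3% to 2% in the MoCA-only setting) and cohorts whose chances differ 2.7-fold at 10% risk per interval. It then judges predictors by an R-squared that reached about .12 on pure noise.

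The sizes depend on assumed decline rates, cohort sizes, candidate numbers and MoCA distribution. The starting-category simulation leaves out CERAD-Plus and FLei. The direction of the R-squared optimism was the same in every setting tried. Attenuation appeared wherever a real effect was simulated, and confounding by follow-up is conditional on predictors differing by cohort.

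**What to change.** For the cognitive-decline outcome, in Cohorts 1 to 3:

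- Replace least squares by a binary or discrete-time model, for example complementary log-log with one row per 8-month interval up to first decline, so that follow-up length enters through the rows.
- Stratify or adjust by baseline category, and preferably also by the continuous baseline MoCA/CERAD-Plus score, because category alone adjusts incompletely.
- Replace R-squared, for both selection and performance, by discrimination and calibration corrected for optimism through cross-validation or bootstrap, with selection repeated inside each resample. Apply the same to the k-nearest-neighbour classifier.
- State that Cohort 4 does not enter this analysis.

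The cost is wording and programming, with no new data. The downside is slightly more analysis work and a lower, more realistic reported performance.

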Furthermore, other motor changes might be used for predicting dementia, e.g., dynamic balance control, finger dexterity, and cutaneous sensitivity*.* Many anatomical structures (e.g., the brainstem, spinal cord, or the primary somatosensory cortex [25–29]), associated with processing cutaneous sensations, are negatively affected in dementia, early dementia, or its precursor MCI. To date, however, there are only few studies which investigate cutaneous sensitivity in MCI patients or dementia diseases [30]. Cutaneous sensitivity is essential for motor performance [31], gait [32], and balance [33]. Quasi-static balance [34] has already been identified as a prodromal marker of dementia [18], whereas dynamic balance with unexpected perturbations has not yet been explored in patients with MCI. Changes in finger dexterity could be predictors for the development of dementia [35], independently from age-related changes [36]. For instance, Rabinowitz and Larner [37] revealed that patients with MCI or dementia show an increase in duration and variability of the finger-touch phase during finger tapping compared to cognitively healthy OA.

Furthermore, neurophysiological techniques, including electroencephalography (EEG), enable detection of functional changes in brain activity at an early stage of dementia [38, 39]. Resting state EEG reveals differences between persons with dementia or pre-clinical dementia and healthy OA [38, 39]. The limited number of longitudinal studies have identified the mean frequency of the total spectrum [40], relative beta power [41], relative alpha power [41–44], relative theta power [40, 42, 45], coherence across all frequencies [40], and coherence in the delta band [46] as possible predictors of cognitive decline. Unfortunately, there is not yet a clear consensus about which parameters best predict dementia or how to translate these findings into cut-offs for individual diagnosis.

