## Methods

### Study aims

The following main research question investigated in this study is:

Which cognitive, sensory, motor, and neurophysiological variables are predictors of the transition from subjective cognitive impairment or MCI to dementia in comparison to age-matched healthy OA?

The objective of the SENDA study is to develop a multi-dimensional sensor-based instrument based on the stated variables or their combination to detect cognitive decline or dementia in OA.

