### Questionnaire battery

Participants need to complete a questionnaire battery, which includes the following secondary outcome parameters: frailty, physical activity, social support, social activities, depression, comorbidities, health behavior, quality of life, and handedness. The self-administered questionnaire contains validated instruments and self-generated items which are shown in Table 4. Sociodemographic information includes age, sex, education, and employment.

**Table 4 Tab4:** Outcome measures in the self-administered questionnaire

Outcome measure	Instrument/scale

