### Expected results

We expect to find several motor, sensory, electroencephalogical, and cognitive prodromal markers for early detection of dementia and its pre-stages. Our assumptions are based on a current literature overview including international and national study results [18, 19, 23, 113].

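### A single regression of cognitive decline cannot separate predictors from mediators, and selecting only its most parsimonious form can attenuate or drop a marker that predicts on its own

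*Protocol article*

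**What the plan says.** Under Statistical analyses, the protocol article gives a multiple regression, with ordinary least squares as an example, a double task: it "is used to detect several predictors or mediators of cognitive decline". The selection rule follows: "To identify the most parsimonious model, and with it the final predictors, we analyze the corresponding coefficients of determination". A correction for multiple comparisons is promised. The same section also plans k-nearest neighbours, mixed-effects models of the motor, sensory, EEG and cognitive parameters over time, and Cox hazard ratios of progression to dementia by decline in each domain.

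Under Study aims, the research question concerns prediction only: "Which cognitive, sensory, motor, and neurophysiological variables are predictors of the transition from subjective cognitive impairment or MCI to dementia". The instrument is to be "based on the stated variables or their combination to detect cognitive decline or dementia in OA". Under Expected results, the authors write: "We expect to find several motor, sensory, electroencephalogical, and cognitive prodromal markers for early detection of dementia and its pre-stages".

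The Background links two of the domains: "Cutaneous sensitivity is essential for motor performance [31], gait [32], and balance [33".

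Table 2 shows T1, T2 and T3 visits only for Cohorts 1 and 2. Cohort 3 stops at T2 and Cohort 4 at T1.

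**The concern.** Two things follow from the two regression sentences read together.

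First, a mediator is defined by a path: the marker affects the mediator, which affects the outcome, in that order in time. A regression of the outcome on both variables estimates only the last step. It contains no model for the mediator and no information on direction. Any statement from this regression that a variable mediates decline would therefore be unsupported.

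Second, a coefficient in a model that also holds a correlated marker answers a different question from the coefficient of the marker alone. It gives what the marker adds once the other is known. If part of a sensory marker's association with decline is shared with gait or balance, that part is credited to the motor marker. A rule that keeps only the smallest adequate model may then leave the sensory marker out of the final predictors. Because the study asks which variables predict decline and hopes to find sensory markers among them, a reader could take that absence to mean that the marker does not predict.

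**Working it through.** **Inputs from the protocol article.** Analysed sample 200, alpha 0.05, power 0.80 (Sample size). One regression, with selection by coefficients of determination (Statistical analyses).

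**Inputs that are assumptions.** Standardised total effect of the sensory marker S on decline: 0.20. Correlation of S with a motor marker M: a = 0.5, varied from 0.2 to 0.7. Share s of the effect that runs through M: 0 to 1. Two-sided test.

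**The plan's own figure.** The required 200 cannot be reproduced uniquely, because no numerical effect size, number of predictors or test family is given. For a single coefficient, f² = 0.04 requires 199, so 200 is plausible. It is not in dispute here. The assumed effect of 0.20 gives f² = 0.04/(1 − 0.04) = 0.0417, close to that value.

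**Step 1: predictor or mediator.** Two structures were compared: S acts on M and M on decline; or M is a common cause of S and of decline. With standardised variables and the same a, b (effect of M) and c (direct effect of S), both give identical correlations among S, M and decline, so the regression fit must be the same. Simulation confirms it (200 participants, 2000 replicates, a = 0.5, s = 0.5): the mean coefficient of S given M is 0.100 with 24% detection in the first structure, and 0.098 with 22% in the second. The difference is simulation error. Nothing in the fitted model identifies which structure is true.

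**Step 2: effect of joint modelling.** Set c = 0.20(1 − s) and b = 0.20s/a. Then:

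- R² of the joint model = b² + c² + 2abc
- gain in R² from adding S to M = c²(1 − a²)
- f² = gain/(1 − R²), noncentrality = 200 f²

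S alone: R² = 0.04, noncentrality 200 × 0.0417 = 8.33, detection 82%.

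Joint model, a = 0.5:

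| Share mediated | c | b | R² | Gain from S | f² | Detection, noncentral F | Detection, simulation |
|---|---|---|---|---|---|---|---|
| 0 | 0.20 | 0 | 0.040 | 0.0300 | 0.0313 | 70% | 69% |
| 0.25 | 0.15 | 0.10 | 0.0475 | 0.0169 | 0.0177 | 47% | 46% |
| 0.50 | 0.10 | 0.20 | 0.070 | 0.0075 | 0.0081 | 24% | 24% |
| 0.75 | 0.05 | 0.30 | 0.1075 | 0.0019 | 0.0021 | 10% | 10% |
| 1 | 0 | 0.40 | 0.160 | 0 | 0 | 5% | 5% |

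In the first row the coefficient is still 0.20. The fall from 82% to about 70% is loss of precision from the correlation alone.

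**Step 3: range.** In the simulation, over correlations from 0.2 to 0.7, detection with half mediated is 35% down to 17%, and with nothing mediated 79% down to 54%. With full mediation it is 5 to 6% for correlations from 0.3 to 0.7. At a correlation of 0.2, full mediation would need b = 0.20/0.2 = 1, which leaves no residual variance, so that cell is impossible.

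**Step 4: relation to the stated rule.** The detection rates come from a 5% coefficient test. The plan selects on coefficients of determination and corrects for multiplicity, which these rates do not model. The R² gain is closer to the stated rule and moves the same way: 0.04 for S alone, against 0.03, 0.0075 and 0 on top of M with none, half and all mediated.

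**The case against.** The strongest reply is that this is a prediction study. For a combined instrument it is proper to drop a marker whose information another carries. That stands, and the joint model should stay for that purpose. It does not cover the mediator claim, nor the further question of which variables predict decline.

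It is also fair that a condensed article leaves entry order, blocks and mediation paths to a fuller plan, and that joint entry of all domains is implied by one parsimonious model rather than stated. A fuller plan could add a mediation analysis. The sentence as printed would still give the task to a method that cannot do it.

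Several stronger readings are tempting but not supported:

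- *The regression removes the earliest markers.* Complete loss occurs only under full mediation; otherwise the coefficient is attenuated. The Background calls cutaneous sensitivity essential for gait and balance. It does not say that sensitivity affects cognition through them; sensory and motor changes may be parallel signs of disease.
- *EEG markers suffer in the same way.* Nothing in the article places EEG upstream of the motor markers.
- *A dropped marker disappears from the study.* The mixed-effects and Cox analyses still cover the sensory and neurophysiological domains. The risk is to the regression's list of final predictors.
- *The confounders contradict the outcome list.* The Questionnaire battery is one "which includes the following secondary outcome parameters: frailty, physical activity, social support, social activities, depression, comorbidities", and the confounders include "comorbidities, psychological status, and social support". A measure listed there may still serve as a covariate, and the article does not say that follow-up values would be adjusted for. Harm from that is hypothetical.

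**Conclusion.** The mediator part of the regression sentence is wrong as written. This rests on no assumed figure: two different structures give the same fit, no path, order or method is named, and the research question asks only for predictors.

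The second part holds as a risk. Taking the final predictors only from the most parsimonious model can attenuate or drop a marker when correlated motor markers are in the same model. The article supplies none of the effect, the correlation or the mediated share, so the true size is unknown. Under the assumptions above, detection falls from about 82% to between 69% and 5%, depending on the share mediated. The direction is the same at every correlation examined; the amount is illustrative only.

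The point is worth correcting before analysis because it changes what the study may conclude and costs little.

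**What to change.** 1. Delete the words on mediators from the regression sentence. Alternatively, limit mediation to a lagged analysis labelled exploratory: marker at T1, mediator at T2, outcome at T3. By Table 2 this is possible only in Cohorts 1 and 2, the only cohorts with at least three visits.
2. Keep the joint parsimonious model for the combined instrument.
3. Beside it, report each domain (sensory, motor, EEG, cognitive) in its own model adjusted for baseline covariates, and state that absence from the joint model does not mean that a marker is not predictive.

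**Cost.** A change of wording and four extra models on data already being collected, to be included in the planned multiplicity control. Mediator claims are dropped, or restricted to a subset whose size cannot be stated because Table 2 gives no cohort sizes. Two of four cohorts should not be read as half of the participants.

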### Cognitive assessments

#### Montreal Cognitive Assessment/ Consortium to Establish a Registry for Alzheimer’s Disease

To identify cognitive decline, we assess global cognition using the MoCA (Montreal Cognitive Assessment [56]) and the CERAD-Plus (Consortium to Establish a Registry for Alzheimer’s Disease [57]) tools. MoCA is a short screening tool for measuring mild cognitive impairment, i.e., in memory, attention, or executive functions. Participants can reach a maximum of 30 points [58]. The cut-off between healthy and mild cognitive impairment is set at 26 in accordance with the recommendations from Nasreddine et al. [56], which means individuals with a score of 25 or lower are considered impaired.

CERAD-Plus is a reliable and valid assessment of Alzheimer’s disease and consists of different neuropsychological tests, such as the Mini-Mental State Examination, verbal fluency, Boston Naming, word list learning, recall and recognition, constructional praxis and recall, and trail making tests A and B [57]. To detect objective cognitive impairments according to CERAD-Plus, we will compare scores in each subtest (excluding MMSE) to the age, education, and gender-controlled reference norms. Following recommendations of the National Institute on Aging-Alzheimer’s Association workgroups on diagnostic guidelines for Alzheimer’s disease [9], performances worse than 1.5 SD below the norm in one or more subtests are considered objective cognitive impairments.

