#### Questionnaire for subjective assessment of mental performance (FLei)

We use the FLei (‘Fragebogen zur geistigen Leistungsfähigkeit’ [59]) to assess subjective cognitive status. The questionnaire employs 30 questions about cognitive challenges in everyday life, including items about executive functions, memory, attention, and 5 control items. Participants are asked to indicate the frequency of these challenges on a scale from 0 (‘never’) to 5 (‘very often’) and a sum score is then calculated (range 0–120). Participants with a score of 31 or higher and no objective cognitive impairment are categorized as only subjectively impaired in their cognition. This cut-off was chosen because 30 points are reached when a participant chooses 1 (‘seldom’) for every item. This is in accordance with data in other studies showing that participants on average score at the lower end of the answer range (for example *M* = 36.3 for OA with objective impairment [60] and *M* = 28.2 for a general population representative sample [61]). After completing data collection, we will also use a data driven approach to determine a suitable cut-off for our sample and, if needed, adjust the assessment of subjective cognitive status.

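### Pooled cognitive decline has very unequal hurdles by starting state, and starting status is not named in the decline or dementia models, so marker effects can be confounded by it

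*Protocol article*

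**What the plan says.** **Outcome.** The section Cognitive status defines one label: "Cognitive decline is defined as a change from CHI to SCI, pMCI, or MCI, as well as a change from SCI to pMCI or MCI", and then a change from pMCI or MCI to dementia. A move from pMCI to MCI is not listed.

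**Hurdles from CHI or SCI.** Any one objective criterion is enough. On the MoCA, "individuals with a score of 25 or lower are considered impaired". On the CERAD-Plus, "performances worse than 1.5 SD below the norm in one or more subtests are considered objective cognitive impairments". From CHI there is also a purely subjective route through the FLei: "Participants with a score of 31 or higher and no objective cognitive impairment are categorized as only subjectively impaired in their cognition".

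**Hurdles from pMCI or MCI.** Only dementia counts. Either "Individuals are categorized as having dementia when they receive a clinical dementia diagnosis outside of the study at any follow-up", or, on the MoCA and CERAD-Plus jointly, "if they score less than 19 points in the MoCA [62] and perform worse than 1.5 SD below the norm in multiple cognitive domains".

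**Analysis.** The section Statistical analyses describes a multiple regression for predictors of cognitive decline, mixed models of marker change in the three groups, and a Cox model for progression to dementia. On adjustment it says: "Several variables are included as potential confounders, such as sex, age, education, comorbidities, psychological status, and social support". The Sample size section bases its calculation on cognitive decline.

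**The concern.** Starting state is linked to both sides of the regression. By definition it sets how hard it is to be counted as declining. It is also expected to go with the markers: the Background reports slower gait and altered finger tapping in MCI, and resting-EEG differences in pre-clinical dementia. A variable related to both predictor and outcome confounds their association.

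Here the two links pull in opposite directions. Poor markers go with pMCI/MCI, where the hurdle is highest. If pMCI/MCI participants therefore decline less often than CHI/SCI participants, a marker that truly precedes decline looks weaker than it is, and a marker with no effect can look protective. For dementia alone, where risk rises with starting impairment, the same omission pushes the other way. The two analyses of the same markers could then disagree for a reason unrelated to the markers. The selection of final predictors for the screening instrument rests on these estimates.

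**Working it through.** The article gives no decline rates, group shares or marker differences, so there is no planned figure to reproduce.

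**1. Asymmetry from the cut-offs alone.** Take two participants with MoCA 26. The CHI participant is counted as declining after losing 26 − 25 = 1 point. The other is pMCI because of one low CERAD-Plus subtest. On study tests, that participant must lose 26 − 18 = 8 points and also show deficits in multiple domains.

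**2. How often each hurdle is crossed with no true change.** This simulation has retest noise only. From the article: MoCA reliability .92, nine listed CERAD-Plus subtests (MMSE excluded), and subtest reliability within the stated .53 to .91 (run at .55 to .90). Assumed: MoCA mean 24.5 to 26, SD 2.7, subtest intercorrelation .3 to .5. At one follow-up, 13 to 24% of CHI/SCI are relabelled pMCI or MCI, against 0.2 to 0.5% of pMCI/MCI meeting the test-based dementia rule. The CHI-to-SCI route and outside diagnoses are left out.

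**3. Effect on a marker's slope.** Assumed: shares 30/20/50% for CHI, SCI and pMCI/MCI; marker SD 1 within state; marker worse by *g* in pMCI/MCI and by *g*/2 in SCI (mean 0.6*g*). For a linear model without status:

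b_pooled = (b_within + C) / (1 + V)

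- V = 0.3(0.6*g*)² + 0.2(0.1*g*)² + 0.5(0.4*g*)² = 0.19*g*²
- C at decline risks 40/30/8% = 0.3(−0.6*g*)(0.40) + 0.2(−0.1*g*)(0.30) + 0.5(0.4*g*)(0.08) = −0.062*g*

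A within-state odds ratio (OR) of 1.50 per SD corresponds to b_within of about 0.060. The simulated columns come from logistic fits and from linear-model power at N = 200.

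| *g* (SD) | b_pooled | ratio to 0.060 | simulated OR, unadjusted / adjusted | power, unadjusted / adjusted |
|---|---|---|---|---|
| 0 | 0.060 | 1.00 | 1.43 / 1.51 | 0.51 / 0.57 |
| 0.3 | (0.060 − 0.0186)/1.0171 = 0.0407 | 0.68 | 1.26 / 1.50 | 0.28 / 0.59 |
| 0.5 | (0.060 − 0.0310)/1.0475 = 0.0277 | 0.46 | 1.18 / 1.50 | 0.16 / 0.58 |
| 0.8 | (0.060 − 0.0496)/1.1216 = 0.0093 | 0.15 | 1.06 / 1.50 | 0.05 / 0.56 |

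The simulated slope ratios were 1.00, 0.67, 0.47 and 0.16. At *g* = 0 the slope is unbiased. The OR of 1.43 there reflects the non-collapsibility of odds ratios, not confounding.

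**4. Milder or equal risks, *g* = 0.5.** At 30/30/15%, C = (−0.054 − 0.006 + 0.030)*g* = −0.030*g*. With b_within = 0.0656, b_pooled = (0.0656 − 0.015)/1.0475 = 0.0483, ratio 0.74; OR 1.32 against 1.49. At 25% in every state, C = 0; OR 1.47 against 1.50.

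**5. A marker with no within-state effect, 40/30/8%.** b_pooled = −0.031/1.0475 = −0.030 at *g* = 0.5 and −0.0496/1.1216 = −0.044 at *g* = 0.8. The simulated ORs are 0.85 and 0.78, so the marker looks protective.

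**6. Dementia alone.** Assumed risks are 1/2/10%, with a logistic model standing in for the Cox model. C = (−0.0018 − 0.0004 + 0.0200)*g* = +0.0178*g*. At *g* = 0.5, with b_within = 0.0207, b_pooled = (0.0207 + 0.0089)/1.0475 = 0.0283, ratio 1.37. The simulated unadjusted ORs are 1.63, 1.72 and 1.82 at *g* = 0.3, 0.5 and 0.8, against about 1.50 adjusted.

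**7. Whether one status-adjusted slope is enough.** In a separate simulation, all CHI/SCI decline was measurement error and 5% of pMCI/MCI reached dementia. The slope per SD of a favourable marker was −.007 pooled and −.029 with status in the model. With the marker's true effect on dementia set to zero, the adjusted slope was still about −.015. About half of the adjusted slope therefore came from CHI/SCI participants near a cut-off being relabelled. Within pMCI/MCI the slope was then near zero, so separate estimates by starting group show the difference.

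**The case against.** **The list is open.** The confounders are given as examples, and a condensed article may leave the full covariate list to a document not shown. This stands: the text does not exclude starting status, and a reader who infers that it does goes too far. What the article does fix is the pooled outcome, and that definition makes this one covariate essential.

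**Starting state appears elsewhere.** The research question is framed by it, the mixed models use the three groups, and cognitive tests are themselves candidate predictors, so the regression may carry part of baseline cognition. This could reduce the bias in the final model. But the mixed models describe marker change, not decline, and a cognitive score retained by model selection does not reliably stand in for status.

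**The outcome form is not stated.** Ordinary least squares and coefficients of determination could point to a continuous cognitive-change score, to which the unequal hurdles would not apply. The only definition of cognitive decline in the article is the change of status, so that is the fair reading.

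**The effect is not always dilution.** A reader might infer that CHI must have the highest decline rate, or that effects are always diluted by some fixed share such as 40 to 70%. The documents support neither. The hurdles are unequal by definition, but the rates are empirical. The bias vanishes if the marker does not differ by status, is slight at equal risks, and reverses for dementia. A percentage measured against a status-adjusted slope also takes as truth a figure that itself contains misclassification (step 7).

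**Conclusion.** The point holds as confounding by starting state. The unequal hurdles and the absence of starting status from the named confounders can be read directly from the article. The direction follows under two conditions: CHI/SCI are counted as declining more often than pMCI/MCI, and the marker is worse in pMCI/MCI. The cut-offs and the cited retest reliabilities make the first plausible, and the Background expects the second. The size cannot be fixed from the documents and ranges from negligible to near-complete loss of a real effect. It rests on assumed decline risks, group shares, marker gaps and MoCA distribution. This is a worthwhile correction to make before analysis; it does not show that the study will miss its markers.

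**What to change.** In Statistical analyses:

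- Enter baseline cognitive status (CHI, SCI, pMCI, MCI) as a factor in the regression of decline and as strata in the Cox model.
- Report marker effects separately by starting group, with CHI/SCI to pMCI/MCI apart from pMCI/MCI to dementia. A single adjusted slope also absorbs measurement-error transitions within CHI/SCI.
- State how a move from pMCI to MCI is handled.
- Add a sensitivity analysis that counts decline from CHI/SCI only when both the MoCA and the CERAD-Plus show it, or when the next visit confirms it.

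No new data are needed, because status is assigned at T1. The cost is three degrees of freedom (four levels less one) and fewer events per transition, so wider intervals. Confirmation is impossible without a later visit. By Table 2, that affects any decline first seen at T2 in Cohort 3, at T3 in Cohort 2 or at T4 in Cohort 1; Cohort 4 has no follow-up.
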